**1. Background**

In 2014, UNAIDS (Joint United Nations Programme on HIV/AIDS) announced the global “90-90-90” strategy, the target being that by 2020, 90% of people living with HIV will have been diagnosed, 90% of these will be on antiretroviral therapy (ART) and 90% of those on ART will have a suppressed viral load.^1^ In South Africa, however, there are estimated to be 6.47 million people living with HIV, with only 53% of these being engaged in care and 26% of those living with HIV being virally suppressed.^2^ Furthermore, retention at 3 years post ART-initiation in sub-Saharan Africa has been estimated at 65%-70%.^3^ As a suppressed viral load depends primarily on adherence, there is a huge need for effective means of retaining large numbers of people taking ART in care, thereby hoping to increase their adherence and suppress their viral load.^4^ One model of community-based adherence support is the ART adherence club. These were locally piloted from 2007 with the aim of assessing whether this group-based, lay-counsellor led service, with an emphasis on social support and adherence, could help address the needs described particularly with regard to retention in care and viral suppression.^5^,^6^ Since the initial pilots, the club model has been scaled up rapidly with more than 400 clubs meeting in the Cape Town metro.^7^ As this model is being scaled-up and implemented rapidly, there is an urgent necessity to further assess its effectiveness.

A large multi-centre cohort study in South Africa found that community-based adherence support in ART programs improved patient attrition (hazard ratio 0.68, 95% CI=0.65-0.72) compared to no community-based adherence support and concluded that community-based programs should be considered for scale-up.^8^ A more recent systematic review, conducted on low- to middle-income countries found that community-based interventions were at least comparable to facility-based interventions in terms of ART adherence and viral suppression.^9^ Although encouraging results, these studies are not locally or adherence club specific.

Locally, implementation of these clubs has been found to be generally successful and popular with clinic staff and patients, with one local study describing a period of 18 months during which a third of clinic patients were de-centralized to clubs.^10^ Overall ART retention in this study was found to be 97.2% at 6 months (95% CI=95.4-97.8) and 93.5% (95%CI=92.2-94.5) at 12 months, and after a year in a club more than 98% of patients remained virally suppressed.^10^ Although there was no suitable comparison group in this study, these retention rates were shown to be well above the estimated retention rates described above and so this study supported continued expansion of the clubs model.

Analytical studies have shown that local adherence clubs decrease both loss-to-follow-up (hazard ratio 0.43, 95% CI=0.21-0.91) and viral rebound (hazard ratio 0.33, 95% CI=0.16-0.67) compared with usual clinic care.^5^ A later study confirmed this association, finding a loss-to-follow-up hazard ratio of 0.33 (95% CI=0.27-0.40) when comparing club care with clinic care.^11^ These comparative studies add more support in favour of the roll-out of the club model.

Adherence clubs have also been shown to be more cost-effective than clinic care, in low- and middle-income countries^9^ and also locally, with one study estimating a cost per patient-year of $300 for clubs vs $374 for clinic care.^12^ Interviewed club patients reported a higher acceptability of club compared to clinic as well as shorter waiting times.^12^ Again this study concluded by supporting scale-up.

So whilst adherence clubs have been shown to be locally implementable, popular (with buy-in by clinic staff and patients) and cost-effective, and community-based interventions have been shown to improve retention, evidence of local adherence club effectiveness in improving viral suppression and retention has only been observationally obtained.^6^ This observational evidence is highly subject to selection bias, with already-adherent patients being over-represented in the club system because of the club eligibility criteria, which includes a suppressed viral load. Even if this selection bias is limited by including viral suppression as a study eligibility criteria, there still remains the possibility of residual confounding in patient factors such as an openness to club-based care and more inherent adherence.^5^

This trial aims to reduce the effect of selection bias and confounders by using a randomised controlled trial design with two arms – those ART patients receiving care in clinic and those receiving care in clubs. The current local standard of care is clinic-based with potential referral to clubs after 6 months on ART if eligible (eligibility criteria differs slightly facility to facility). In this trial we aim to assess the effectiveness of clubs in achieving retention and a suppressed viral load, amongst other outcomes, by comparing early club referral (at 4 months post-ART initiation) and delayed club referral (after 12 months post-ART initiation). By doing this we hope to generate robust evidence regarding both the effectiveness of clubs and the optimal timing of club referral.

**2. Study Aims and Objectives**

The overall aim of this project is to evaluate the adherence club model compared to the clinic model of care. The two arms of the study will be early referral to the adherence club service (referral by study at 4 months post-initiation) and delayed referral to clubs (after 12 months post-initiation, referral to be done as per usual procedures).

- Primary objective

To compare adult HIV viral suppression up to 12 months post ART-initiation, among adults on ART with a suppressed viral load at 4 months, in those referred to the adherence club at 4 months, compared to those referred to the club after 12 months post-initiation.

- Secondary objectives

To compare the timing of entry into ART clubs, looking at outcomes such as:

- Retention in care ie missed visits and loss to follow-up
- Physical and mental health
- Acceptability of the ART service

This trial is a sub-study of the UCT PACART trial currently underway and as such the setting, population, study design, data management, ethical considerations and internal monitoring systems are designed to be in line with the PACART protocol as much as possible.

**3. Study Design**

Overview

We propose to address these objectives by conducting a pragmatic, two-arm randomised controlled trial to evaluate two different entry points into ART clubs (hereafter referred to as clubs) – at 4 months post-initiation of ART (early) and after 12 months post-initiation of ART (delayed). All adults have a routine clinic visit 4 months post-initiation of ART, for a clinical check-up and viral load testing. Adults attending this visit will be approached by a study recruiter to participate in the trial. If interested in the study and potentially eligible (with the exception of the as yet unknown viral load result), a return visit 1 week later will be arranged to see a member of study staff who will check for a suppressed viral load (<400) and complete enrolment procedures. A total of 214 consenting adults will be randomised to either:

1. Early referral to clubs (at 4 months post-initiation)
2. Delayed referral to clubs (after 12 months post-initiation)

Participants in both arms will be asked to attend 3 study measurement visits in total: at enrolment, and then at4 months and 8 months post-enrolment. These visits will be conducted separately from ART service appointments. Details of study measurement visits are provided in section 7 below. Follow-up of outcomes will be through to 8 months post-enrolment. Participation will impact only on the setting and timing of ART services and will not affect access to care. See below for the study schema:

HIV-positive adults on ART seen at 4 months post-ART initiation at the ART clinic, Gugulethu

**Screening and Informed Consent**

Enrolment of eligible adults, questionnaire administration and phlebotomy for viral load testing

**Randomisation**

**Delayed referral**

Referral to ART clubs after 12 months post-initiation

**Early referral**

Referral to ART clubs at 4 months post-initiation

Setting

The proposed trial will take place at Gugulethu ART clinic in Cape Town and at the associated off-site ART clubs. HIV prevention and treatment services at these facilities have been supported by the University of Cape Town since 2001, and UCT has a dedicated research space for trials on the Gugulethu CHC premises.

Gugulethu has a population of approximately 400000 and is predominantly of low-socioeconomic status. The vast majority of the population uses free local public sector health services. By the end of July 2016, approximately 5259 adults on ART were under the care of the ART services at the Gugulethu Community Health Centre (from which the clinics and clubs are run), with approximately 54% of these being retained in care at the ART clubs (from local data). Since the implementation of clubs at Gugulethu in June 2012, the number of adults retained in club care is steadily increasing. From January 2014 until August 2016, the number of adults retained in club care increased from 2420 to 2850 (from local data).

**4. Study Population**

Participants will be consecutive consenting HIV-positive adults on ART who are seeking care at the Gugulethu ART clinic.

Inclusion criteria

- Age 18 years or older
- Documented HIV infection with ART initiation 4 months ago
- Suppressed viral load at 4 months post-initiation (<400 copies/ml)
- All other month 4 blood results within normal limits
- Willingness to be randomised and return for study measurement visits
- Able and willing to attend service visits at either the clinic or a club
- Able to provide informed consent for research

Exclusion criteria

- Intention to relocate out of Cape Town permanently during the study period
- Any medical, psychiatric or social condition which in the opinion of the investigators would affect the ability to consent and/or participate in the study
- Pregnant
- Current co-morbidity requiring additional health care, either acutely eg tuberculosis or chronically eg hypertension

**5. Recruitment and Enrolment**

Recruitment

This will take place at the Gugulethu ART clinic. Consecutive potentially eligible adults will be approached during their routine 4-month post ART initiation clinic visit, which consists of viral load testing, either directly by the study recruiter or via the attending clinician (who will refer to the study recruiter subject to patient agreement). The potential participant will be given information about the study. If interested and eligible (with the exception of the as-yet unknown viral blood result) they will be given a study visit 1 week later to receive their viral load results from a member of study staff, conclude enrolment procedures and undergo randomisation. At the point of leaving the clinic after their blood test, the potential participant should have the following in place:

- A study visit date for 1 weeks’ time
- A clinic date for 1 months’ time (as per clinic standard of care)
- 1 month of ART (as per clinic standard of care)
- Having had their month 4 blood test, consisting of viral load and safety bloods (as per clinic standard of care)
- Having seen a clinician (as per clinic standard of care)

Enrolment

Enrolment will take place at this follow-up visit (1 week after the month 4 clinical visit), if eligible and consenting. The individual will be informed of his/her viral load result by study staff and, if the viral load is less than 400 copies/ml, he or she will be further screened for eligibility as per the inclusion and exclusion criteria described above. Adults who are deemed eligible and agree to participate will undertake the informed consent process, which will be conducted in a private room by a study interviewer.

Informed consent

Informed consent procedures are outlined in Section 10, below. Trained study staff will ensure that individuals are aware of their right to refuse to participate in the study or to withdraw from the study at any time once enrolled. In addition, study staff will emphasize that all study activities are entirely separate from routine ART care services and that refusal to participate in or withdrawal from the study will have no effect on access to any services provided at public sector health facilities. Moreover, staff will be sure participants understand that their access to ART and any other aspect of their care, will not be affected by their decision to participate. Following, informed consent procedures, enrolled participants will be randomized to either early club referral or delayed club referral.

Recruitment will take place over a 12-18 month period.

**6. The standard ART Services at Gugulethu CHC – the clinic and the clubs**

The local standard of care is clinic-based from ART-initiation, with potential club referral from 6 months post-initiation for those patients who are virally suppressed and have no co-morbidities that require additional health care. Club referral is at the clinician’s discretion. The two models of care are described below:

Clinic care

The standard ART clinic service includes 2-6 monthly clinician reviews and medication refills (according to clinician discretion). Over the December/January holidays, patients receive 3 months of medication from the pharmacy (from mid-October to mid-November). Patients may send someone to collect their medication (“a buddy”) on their behalf. Patients with particular clinical or psychosocial concerns may be reviewed more regularly, or referred to higher levels of care. Patients in the clinic receive a waiting room health promotion and adherence talk (held daily). Standard clinic care includes blood tests at month 12 post-initiation (viral load and ART safety bloods as needed). There is no immediate follow-up for clinic defaulters, although every 4 months a list of those lost to follow-up is generated via the eKapa computer system, and those on the list will be visited at home depending on resources.

Club care

There are currently 127 Adherence clubs operating at Gugulethu CHC. They meet in the nearby off-site community hall iKhwezi. Each club meets 2 monthly with the exception of the December/January holidays whereby the appointment interval is 4 months. The clubs are run by club counsellors who give a health promotion and adherence talk, promote condom use, weigh and check symptoms for each club member and dispense 2 months of pre-packed ART (4 months over the December/January holiday period). Each club receives an annual blood test visit at which point a nurse practitioner performs routine phlebotomy. The following visit is a clinical visit, at which the nurse practitioner checks the blood results and performs a clinical assessment. Patients in clubs may send someone (”a buddy”) to collect their ARTs for them, but only every alternate visit and never on a blood or clinical visit. If a participant misses a club visit, there is a grace period of 5 working days after the scheduled session for them to collect their medication. Those who have not collected their medication within this period are identified as defaulters. These defaulters are followed up by the counsellors via phone calls and home visits, depending on resources, and are removed from club. Patients are also removed from club if they have a high viral load (>400 copies/ml), are pregnant, or have any symptoms meriting further clinical assessment.

A comparison of clinic and club care is tabulated below:

| **AREAS OF CARE** | **MODEL OF CARE** (August 2016) |  |
| --- | --- | --- |
|  | **CLINIC** | **CLUB** |
| **Summary of model** | Seen in the Gugulethu ART clinic | Seen in an offsite hall, iKhwezi, as part of a club |
| **Usual eligibility criteria** | None – all patients on ARTs may attend | >6 months on ART, viral load<400, no other co-morbidities |
| **First appointment date** | Patients with a referral letter can present on any day. Date does not have to be booked with clinic | Patients referred to club must present to the club office, which is located at the clinic, with their clinic folder and referral letter. A counsellor then provides a date for the first visit, slotting the patient into a club with space available. |
| **Attending staff** | Clinician - CNP or doctor | Counsellor. CNP twice a year (blood visit and clinical visit) |
| **Prescription frequency** | 1-6 monthly, depending on clinician discretion | 2 monthly |
| **Christmas holiday arrangments** | Pharmacy dispenses 3 months of ART from mid-October | Pharmacy dispenses 4 months of ART from the beginning of October. |
| **Buddy collections** | Buddies are unmonitored and are able to collect medication on behalf of the patient except when a clinician specifically requests to see the patient. | Buddies are able to collect medication on behalf of the patient on alternate visits, but blood and clinical visits must be attended by the patient. |
| **Counselling (lifestyle and adherence)** | Daily waiting room counsellor talk. Selected (high risk for non-adherence) patients receive pill checks and further counselling | Every club visit |
| **Blood tests** | CD4 annually only if CD4<200 | CD4 annually only if CD4<200 |
|  | Viral load (VL) at month 4, 12 and annually if on first-line regimen.  VL at month 6, 12 and annually if on second-line regimen.  If on tenofovir, creatinine is checked at month 1, 4, 12 and then annually.  If on zidovudine, Hb and differential white cell count is taken at month 1, 2, 3 and 6.  If on aluvia, cholesterol and triglyceride checked at month 3 and yearly if indicated. | VL annually, timing depends on when club blood visit scheduled.  If on tenofovir, creatinine is checked annually.  If on aluvia, cholesterol and triglyceride checked annually if indicated. |
| **Time spent at the location** | Varies from around 2 hours to the whole day. | 1-2 hours. Max around 3 hours for a clinical visit. |
| **Non-attenders follow-up** | Every 4 months, those patients who have not had an ART refill are visited at home by CCWs | Those who don't collect their medication within the 5 day grace period are called and visited (if resources allow) |
| **Procedure for VL 400-1000** | Repeat VL after 6 months | Referred back to clinic, then usual clinic protocols followed |
| **Procedure for VL >1000** | Refer to ROTF service | Referred back to clinic, then usual clinic protocols followed |

**7. Research Procedures**

Randomisation

Randomisation will be performed once enrolment is completed. Randomization will be a 1:1 allocation using a dynamic permuted block design generated by an independent statistician. Randomization numbers will be generated prior to the start of the study, and placed in sequentially numbered opaque envelopes. Randomization envelopes will be stored in a locked and restricted access cabinet in the research clinic that will be accessed by the study coordinator when a participant is fully consented and has been enrolled in the study. There will be independent documentation of the participant identification number, randomization date, and randomization assignment. The study coordinator involved in randomization will not be involved in interviewing participants. The allocation to either early or delayed adherence club referral will be conveyed to both the participant and to the study recruiter.

Early referral arm

The participant will be escorted by study staff straight from enrolment to the club office for referral to the club service. Here, a club counsellor will educate them about the club system and rules, enrol them into a club and give them a club appointment date within 2 months. If more ART will be needed before the date is reached, a study clinician will dispense. The specific club group to which the individual is assigned will depend on space availability within groups. Participants will be allocated to groups non-purposively, and there will be no attempt to cluster participants within a single group. Their clinic appointment, in 1 months’ time for viral load results, will be cancelled.

Delayed referral arm

Individuals randomized to this arm will be seen at the clinic, with no club referral to be done before 12 months post-initiation. After 12 months has elapsed after initiation, the participant will be subject to usual clinic procedures which may include referral to clubs, dependent on the attending clinician as per standard of care.

The participant’s folder will be labelled with a sticker, signifying no referral to the club service to be done by the clinic staff. Those allocated to the delayed referral arm will also have their names entered onto a list to be held by the senior club counsellor and kept in the club office. This list will be checked when participants are referred to the club office and any participants on this list will not be given a club date and will be referred back to the attending clinician

Study visits

Including enrolment (study visit 1), there will be 3 study visits. These will be at enrolment and then at4 months and 8 months post-enrolment.

Measurements will be carried out by a study measurement team comprised of a research nurse and interviewers who operate separately from the routine ART services (adherence clubs and clinic). Visits will take place in a dedicated research space. The separation of routine services from study services will facilitate masking of trial assessments and retention activities.

At each study visit (estimated to last 1-2 hours), a standardized questionnaire will be used by the study interviewers to collect information and phlebotomy will be performed.

**At the enrolment visit and all subsequent study visits**, information will be collected on: demographics, past medical history and health care use, HIV disclosure, current ART use, relationship with health providers, mental health, alcohol and substance use, and social impact.

**Phlebotomy** will involve drawing 5ml of venous blood for storage and batched viral load testing. This same blood will be used (via pipetting from the PPT blood tube) for Dried Blood Spots (DBS). This pipetting method will be used to avoid a further procedure and its incumbent risks.

Laboratory measures

Participant venous blood (approximately 5ml at up to 3 study visits, totalling a maximum of 15ml over 8 months) will be drawn (using an PPT tube) at every study measurement visit. As previously described, some of this blood will be stored as a Dried Blood Spot, for use as an objective marker of adherence. The PPT tube specimen will be transported to the National Health Laboratory Service (NHLS) for testing.

The venous blood collected will be used for HIV viral load batch testing (Abbott Molecular RealTime HIV-1 assay, Abbott Molecular, Illinois, USA). Following VL testing the remaining plasma will be stored as single aliquots of $\pm80\mu l$ in Sarstedt screw cap tubes in a -80°C freezer at the School of Public Health and Family Medicine, UCT. The DBS cards will be transported for storage at -80 °C (subject to consent). These stored specimens will be for future research use.

All phlebotomy, specimen handling, specimen processing, and specimen storage will take place using routine protocols. Note that the laboratory measures taken for study measurements are in addition to routine laboratory tests taken for HIV care and treatment.

Data abstraction

In addition to the study measures described above, routine clinical care record reviews will be conducted in order to collect key data on participants regarding ART initiation and follow-up. Permission to review clinical records of participants, is included in informed consent documents for all participants. The records used will be those at the clinic and club as needed.

Items to be abstracted include: date of HIV diagnosis, date of initial presentation to the ART service, pre-ART clinical history, examination and laboratory investigations (including TB-related history and WHO staging), date of ART initiation, dates of routine follow-up visits attended post-ART initiation, major clinical events post-ART initiation and ART side-effects.

All data abstraction will take place with the written permission of (a) the participant (via informed consent), (b) the research oversight body of the Government of the Western Cape (GWC), (c) the participating REC, and (d) the facility manager of the health facility. Data abstraction will be conducted by trained staff working under the close supervision of the project coordinator. All data will be abstracted from the clinical record onto separate forms that include record of the type of documentation, the date of abstraction, and the name of the individual abstracting data.

All data collection is confidential, with records identified via participant folder numbers only. No participant names are recorded on study documents.

In addition to this data abstraction, permission to review clinical records of participants, including those at government clinics and hospitals within the Western Cape for up to 3 years after enrolment, is included in informed consent documents for all participants.

The health data will be aes-encrypted and password protected, and will be transferred using a secure file transfer service such as filesender. Identifying information and clinical information will be stored and transferred in separate files.

Identification of health care needs during study procedures

At every study measurement visit, any individual found to have an unmet health need (whether physical or mental) will be referred to the relevant service within the Gugulethu CHC or at higher levels of care, as appropriate. In particular, any individual found to be non-adherent to ART during the study will be referred to clinic staff for adherence counselling and then to the relevant ART service as per randomization assignment.

Staff Training

Prior to the initiation of the study, all staff who will have contact with participants will take part in a study-specific training. The curriculum of the training will include: rationale, purpose, and scientific objectives of the study; study design and methodology; conduct of study assessments, tracking of participants, completion of study forms, and data collection; staff responsibilities; recruiting participants; procedures for enrolling participants into the study; randomization, universal precautions, communication skills, safety in the field, ethical guidelines for research including participants’ rights; procedures for obtaining informed consent; and confidentiality requirements. There will also be training on adherence assessment and referral for those participants admitting poor adherence.

Study staff will receive hands-on training that will include an introduction to data collection forms and procedures. Mock interviews will be an essential component of the training and protocol team members will act as both the trainer and the mock respondent. The trainer will take the staff through each step of the data collection process, from enrolling participants to ending the study visit and completing the necessary forms. Study staff will be given a chance to practice both the English and isiXhosa versions of all the assessments in order to discuss and resolve any issues. Training for study staff is expected to take approximately 1 week with additional follow-up training, as necessary.

All staff who, through the course of their work, will have knowledge of, or access to, personal information about participants will be required to complete training on patient confidentiality and sign a confidentiality agreement before the start of data collection.

Study staff members who will collect blood samples and conduct laboratory analyses will receive training in universal precautions, sample collection, testing of study samples and on the SOPs in phlebotomy and DBS.

In addition, staff will be trained in the management of crisis situations, including reports of abuse and domestic violence that may be disclosed during study participation. The site will have established procedures for managing these situations including counselling and appropriate referrals. Procedures for managing these situations will be outlined in study SOPs.

For all study staff, there will be additional training days scheduled during the study for refresher training. During these refresher trainings, study staff will review study procedures and discuss any challenges encountered

Contamination and masking

Contamination between groups is a concern but blinding participants to this type of health systems evaluation is not possible. Contamination in this case means that participants in the delayed referral group may be aware of the early referral group participants who are already in the adherence club system, and vice versa, so potentially changing their behaviours related to their own ART use and retention in care

Detection biases are possible for self-reported outcomes due to lack of masking, but the primary outcome (a suppressed viral load) is objective. We will conduct the study measurement visits from a space at the Gugulethu CHC that is separate from both the general adult ART services and the adherence club service, with study staff who are different from participants’ service provider, in order to minimize possible biases in assessment. We will also blind data analysis by the coding of study arm until the main trial analysis is complete and approved by the investigator team.

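### Each allocation is told to the study recruiter at a single unmasked site with permuted blocks, so some upcoming allocations could be guessed, mainly at the enrolment visit

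*Combined protocol and SAP*

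**What the plan says.** **Who learns the allocation.** Section 7, Randomisation: "The allocation to either early or delayed adherence club referral will be conveyed to both the participant and to the study recruiter".

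**Who approaches patients.** Section 3, Overview: "Adults attending this visit will be approached by a study recruiter to participate in the trial". Section 5 adds a second route, so the approach is made "either directly by the study recruiter or via the attending clinician", and sets a consecutive rule: "Consecutive potentially eligible adults will be approached during their routine 4-month post ART initiation clinic visit".

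**When enrolment and randomisation happen.** Section 5: "Enrolment will take place at this follow-up visit (1 week after the month 4 clinical visit), if eligible and consenting". Sections 3 and 5 give the viral load check and enrolment to study staff without naming the role. Section 5 has an interviewer conduct consent. Neither section says whether the recruiter may also fill these roles.

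**How the sequence is made.** Section 7: "Randomization will be a 1:1 allocation using a dynamic permuted block design generated by an independent statistician". No block size is given, the word 'dynamic' is not explained, and nothing says that block sizes are kept from site staff. Section 3 (Setting) describes one ART clinic, no stratification is stated, and section 7 (Contamination and masking) accepts that participants cannot be blinded.

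**Safeguards.** Also in section 7: the list is prepared before the trial and placed in numbered, opaque envelopes in a locked cabinet. The study coordinator opens an envelope only after consent and enrolment are complete, and takes no part in interviews. Assignments are documented independently.

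**The concern.** Envelopes protect the next allocation from being seen. They do not protect it from being inferred. In a permuted-block list at one unstratified site, the arm that is behind within the current block is more likely to come next, and near the end of a block the next allocation may be certain. Anyone who is told every past allocation can keep that count.

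If that person also influences who is approached, found eligible or encouraged to consent, the patients entering the two arms can differ systematically. Section 1 criticises the earlier observational evidence for this kind of selection: patients in clubs may be more open to club care and inherently more adherent. Removing it is the stated reason for randomising. Measured covariates capture such traits only partly, so the model adjustment in section 9 could not be relied on to repair selective enrolment.

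**Working it through.** The plan gives no figure for predictability, so there is none to reproduce. The check asks how often a best guess of the next arm is right, at two moments: the enrolment visit and the approach one week earlier.

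**Inputs from the documents.** 1:1 permuted blocks (section 7); 214 participants (section 9); recruitment over 12–18 months (section 5); one week from approach to enrolment (sections 3 and 5).

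**Assumptions.** Fixed blocks of 2 to 10, or random mixes of small sizes; even accrual; patients enrolled in the order in which they were approached; all past allocations known and, for fixed blocks, the block size known.

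**Allocations falling within the one-week gap.** 214/52 weeks = 4.1 per week for 12 months; 214/78 weeks = 2.7 per week for 18 months. So about 3 to 4.

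**Formula for fixed blocks.** Let the block size be s, with h = s/2 per arm. If m allocations of the current block are known and a of them are early referral, the best guess is right with probability max(h − a, h − m + a)/(s − m). The chance of that history is C(h,a)·C(h,m − a)/C(s,m). For position k in the block with L unseen allocations in between, m = k − 1 − L; if m ≤ 0 the guess is a coin toss. Average over all positions.

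*Blocks of 4, L = 0 (enrolment visit).* The four positions give 1/2, 2/3, (1/3)(1) + (2/3)(1/2) = 2/3, and 1. The sum is 2.833, and 2.833/4 = 0.708. The allocation is certain at position 3 with probability 1/3 and always at position 4, so (1/3 + 1)/4 = 0.333.

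*Blocks of 6, L = 3 (approach).* Positions 1–4 give 0.5 each. Position 5 (m = 1) gives 3/5 = 0.6. Position 6 (m = 2) gives 0.4 × 3/4 + 0.6 × 1/2 = 0.6. The sum is 3.2, and 3.2/6 = 0.533.

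The random mixes were simulated: 1,500 runs of 214 allocations, always guessing the arm that is behind in the running count and tossing a coin when level.

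| Assumed scheme | Certain, L = 0 | Correct, L = 0 | L = 1 | L = 3 | L = 4 |
| --- | --- | --- | --- | --- | --- |
| Fixed 2 | 50% | 75.0% | 50.0% | 50.0% | 50.0% |
| Fixed 4 | 33% | 70.8% | 58.3% | 50.0% | 50.0% |
| Fixed 6 | 25% | 68.3% | 60.0% | 53.3% | 51.7% |
| Fixed 8 | 20% | 66.6% | 60.4% | 55.0% | 53.4% |
| Fixed 10 | 17% | 65.3% | 60.3% | 55.9% | 54.4% |
| Mix 2/4 | – | 72.2% | 55.5% | 50.0% | 50.1% |
| Mix 2/4/6 | – | 70.2% | 57.7% | 51.7% | 50.8% |
| Mix 4/6 | – | 69.2% | 59.3% | 51.9% | 51.0% |
| Mix 4/6/8 | – | 68.0% | 59.8% | 53.3% | 52.0% |

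At the enrolment visit (L = 0) the guess is right 65–75% of the time. At approach, with 3 to 4 allocations in between, it is right about 50–55% of the time. If only one lies in between, it reaches about 60% at most. Varying the block size does not by itself lower the L = 0 figure much: the mixes still give 68–72%, and their guessing rule uses only the running count.

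**The case against.** A reader might infer that the recruiter can predict upcoming allocations when deciding whom to approach, and so recruit selectively. The documents do not support that. The recruiter acts a week before randomisation, and at the planned accrual the intervening allocations bring the guess close to chance. The consecutive rule limits discretion over whom to approach, and some patients come through the attending clinician.

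A reader might also attribute the discretionary eligibility judgement to the recruiter. The exclusion "Any medical, psychiatric or social condition which in the opinion of the investigators would affect the ability to consent" leaves it to the investigators. Consent is taken by an interviewer, and nothing in section 7 says that those who screen or consent are told allocations. This objection stands in part: the exposure at enrolment requires that the recruiter, or someone who shares the recruiter's knowledge, is involved in that visit. The documents neither say so nor exclude it.

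Nor does the phrase "dynamic permuted block design" contradict a list sealed in advance. Varying block sizes can be generated beforehand and put in envelopes. The word is ambiguous, and block sizes may be withheld in practice without the protocol saying so.

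Finally, guessing accuracy is not bias. There is no evidence of motive or of selective behaviour, every entrant must have a suppressed viral load, and the safeguards in section 7 are real. All of this lowers the risk. It does not answer the narrower point: the plan makes it a rule to give the allocation history to a recruiting role, with no statement that keeps that role away from final screening.

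**Conclusion.** The concern holds in a limited form. The plan routinely tells past allocations to the role that approaches later patients, at one unmasked site with permuted blocks of unstated size. Some upcoming allocations could therefore be guessed, mainly at the enrolment visit: about 65–75% correct against 50% by chance for fixed blocks of 10 down to 2, with 17–50% of allocations certain. At the approach a week earlier the figure is about 50–55%.

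These figures rest on assumed block sizes, full knowledge of past allocations and of the block size, even accrual of 214 participants over 12–18 months, and enrolment in order of approach. The independent statistician, the opaque envelopes, opening only after consent, and consecutive approach reduce the risk without removing it. No effect on the treatment estimate can be calculated, and the documents do not show that selection would occur. The sample size is unaffected. The change is worth making because it is cheap and protects the main purpose of randomising.

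**What to change.** In section 7 (Randomisation), replace the sentence on conveying the allocation with:

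> The study coordinator will convey the allocation to the participant and only to the staff who escort early-arm participants or label folders. Staff who approach, screen or consent patients will not be told allocations.

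In place of the word 'dynamic', state that block sizes vary at random and are known only to the independent statistician. The first change matters more. The second removes most of the certainty about the ends of blocks but leaves the running count informative to anyone who has it.

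A log of all consecutive patients approached, with reasons for exclusion or refusal, would be a useful addition because it would make selective enrolment detectable.

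The cost is a few protocol sentences and a task split within existing staff, whose numbers the documents do not give. Some visibility would remain: early-arm participants are escorted to the club office, and delayed-arm folders carry a sticker.
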